#### Software

Data management and analyses described above will be conducted using R [125] and Statistical Package for Social Science (SPSS) (Version 25) [126].

## Discussion

It is now evident that perinatal AD are highly prevalent (1 in 5 perinatal people), impairing, distressing with potential negative effects for the developing fetus and infant [15–17]. Detection, prevention, and treatment are highly important to mitigating these consequences. Accurate and reliable screening is a critical first step to identifying those at risk of, or currently suffering from, these disorders. Despite calls for implementation [62, 64], perinatal AD screening is rarely conducted. This is in large part because the current published literature fails to provide sufficient empirical support for any instrument. Although much research evaluating perinatal AD screening tools has been conducted, it has been hampered by methodological shortcomings of such magnitude that no available screening tool can justifiably be recommended for widespread implementation.

For these reasons we have undertaken a large-scale study of the accuracy of a broad range of potential perinatal AD screening tools. Our objective is to identify, employing gold standard methodology, one or more accurate and reliable measures. We have sought to overcome the methodological shortcomings of previous research so that our findings can be justifiably used to make practice and policy decisions. Population-based administration of screening tools is expensive to implement and is unlikely to be undertaken without strong evidence that the screening tool(s) employed will in fact correctly identify those experiencing the disorders being screened for.

To our knowledge, this will be the first study in which all gold standard methodology has been employed. Specifically, in this research:all of the core anxiety disorders and additional anxiety-related disorders are assessed;gold standard, diagnostic interviews are administered;diagnostic assessments are conducted blind to screening tool results;DSM-5 diagnostic criteria are employed;an unselected/representative sample of pregnant and postpartum people is being sought;screening accuracy is assessed in both pregnancy and the postpartum; anddiagnostic interviews are administered within two to six weeks of completion of screening tools.

The study includes a number of additional methodological strengths. Specifically, the study is powered to ensure we can assess the accuracy of included screening tools both for the AD as a whole, but also for each individual AD. Our approach to recruitment is designed to result in data for 1,000 pregnant and 1,000 postpartum people. We are over-sampling, where needed, perinatal people with specific AD so that we are able to report on screening accuracy for each of the individual AD.

Beyond the core goal of this research (i.e., to assess the accuracy of various self-report measures when used as screening tools for perinatal AD), we have the opportunity to explore a number of additional research questions. For example, because this research is based on DSM-5 anxiety and related disorders, we are also able to explore screening for separation anxiety disorder. To our knowledge, no findings related to screening for adult separation anxiety among perinatal people have been published. In addition to providing information about screening accuracy for adult separation anxiety disorder, we will also be able to provide the first estimate of the prevalence and incidence of this condition among perinatal people. Further, we will document the point prevalence and postpartum incidence of perinatal AD in pregnancy and the postpartum. To our knowledge, perinatal AD prevalence, based on DSM-5 criteria has yet to be reported. Further, we will be able to assess the extent to which participants who report symptoms meeting criteria for one or more AD go on to receive an assessment and treatment for these conditions. We will also assess various predictors (e.g., demographic, reproductive, identity, experience of discrimination) of perinatal AD symptoms and diagnosis, as well as assessment and treatment access and utilization. Finally, we will assess the relationship between the burden and gender distribution of unpaid domestic labour (i.e., household chores and childcare responsibilities) and mental health.

Findings from this research will provide rich data to answer not only our core research questions but additional, important questions pertaining to perinatal AD.

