Routine screening for perinatal depression is employed in many parts of the world [40–42]. This has been made possible through the availability of screening tools for perinatal depression of high and well-established accuracy [43, 44]. Despite the fact that, among perinatal people, AD are significantly more common that perinatal depression (21% for perinatal AD, and approximately 6% for perinatal depression) [15, 45] screening for these conditions is almost non-existent [4]. This is largely the result of a lack of identifiable screening tools with established and high accuracy [46]. Numerous self-report screening tools for perinatal AD have been developed and to some extent evaluated [47]. More than one may, in fact, prove to be highly accurate. However, assessments of their accuracy have been burdened by methodological weaknesses of sufficient magnitude such that, at present, no screening tool for perinatal AD can be recommended with confidence [48].

What makes the establishment of broadly disseminated screening for perinatal AD so appealing is the following. First, perinatal people are highly accepting of screening programs, but tend not to discuss their mental health difficulties unless asked about them [4, 49]. Consequently, without screening, perinatal AD will often go undetected [50]. Second is the recent increase in the availability and acceptability of highly effective, evidence-based treatments for perinatal AD. Specifically, cognitive behaviour therapy (CBT), a form of talk therapy, is the treatment of choice for many anxiety-related conditions. Randomized controlled trials comparing CBT with medication approaches have found that CBT is safe and equal or superior to medication [51–53], and a recent systematic review found CBT to effective for perinatal populations [54]. Historically, access to CBT has been limited and not broadly publicly funded due to the fact that it is time-consuming and expensive [55–57]. More recently, however, CBT has become increasingly available in self-administered and online formats, greatly improving accessibility [58, 59], without any loss in effectiveness [60, 61]. Accordingly, when screening leads to appropriate treatment, positive outcomes are highly likely.

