### Inclusion criteria

All pregnant individuals, living in the province of British Columbia (BC), over the age of 18 and able to speak and read English at a level sufficient to complete the study questionnaires and interviews are eligible to participate in this research.

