### Sample size estimation

Approximately 44,000 residents of BC give birth each year [86]. We are seeking a sample of 1,000 participants for each of the two study time points. This will provide 80% power to detect AUC for ROC curves ≥ 0.56 as significantly different from 0.5, at a significance level = 0.05; 88% power to detect sensitivity ≥ 0.60 as > than 0.5; and > 99% power to detect specificity ≥ 0.60 as > 0.5. We will be able to estimate the prevalence of low prevalence conditions (e.g., 3%) with 1.5% margin of error and 95% confidence. Of note, we will have 80% power to detect AUC ≥ 0.65; 80% power to detect sensitivity ≥ 0.72; and 99% power to detect specificity ≥ 0.72. Allowing for an anticipated attrition of 15%, we are seeking to recruit 1,200 participants. To have 80% power to detect sensitivity ≥ 0.7; and 99% power to detect specificity ≥ 0.6 for the individual AD, we will need ≥ 30 participants per AD in this sample.

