### Data analysis plan

#### Descriptive statistics

Descriptive information will be presented as means, standard deviations, percentages, and 95% confidence intervals. The diagnostic accuracy of screening tools will be assessed via receiver operating characteristic (ROC) curve analyses within the prevalence sample. AUC values, derived from the ROC curves, represent overall diagnostic accuracy, and will be reported with 95% confidence intervals. Optimal cut-off values for each measure will be determined from ROC analyses and based on maximizing Youden’s *J* index value (see screening tool metrics above). The sensitivity, specificity, PPV and NPV, LR ± , and percent correct classification will also be reported. We will also determine the cut-point associated with 0.75 sensitivity and calculate the corresponding *J* index and specificity (prevalence sample). We will estimate sensitivity and specificity of each of the screening tools for the individual AD.

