#### Research objectives

AUC will be compared among all pairwise combinations of tools using DeLong’s method for paired ROC curves [123] and using a false-discovery-rate correction (FDR, with family-wise alpha = 0.05) for *p*-values [124] to account for multiple testing. Sensitivity and specificity will be compared across all tools using McNemar’s test for paired categorical data, with FDR correction for multiple testing [124].

We will report the full composite of the screening tool metrics (i.e., AUC, *J* index, PPV, NPV, LR + , and LR-) for each of the measures assessed. Screening metrics will be reported for the core AD with and without PTSD and OCD, as well as separately for major ethnic and parity groups (i.e., parity = 0, and parity ≥ 1). We will recommend screening tools based on their accuracy (i.e., scores on the above metrics) and implementation feasibility (i.e., length, administration time, scoring time and complexity, and cost, if any). To ensure the screening tools are not missing any individual AD by analyzing them together, we will also estimate sensitivity and specificity for each AD by comparing those who report symptoms meeting criteria for one specific AD with those whose symptoms fail to meet criteria for any AD.

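### Power for each individual AD is claimed outright, but it depends on 30 cases per AD, which 1,000 people do not secure for less common disorders, and 30 cases fall short of 80% power at sensitivity 0.70

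*Protocol article*

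**What the plan says.** Under Sample size estimation the target is stated as "We are seeking a sample of 1,000 participants for each of the two study time points", and then "Allowing for an anticipated attrition of 15%, we are seeking to recruit 1,200 participants". The section gives the power for the AD as a group and for a lower-prevalence case. It ends with a requirement for individual disorders: 80% power for sensitivity of at least 0.7 and 99% power for specificity of at least 0.6 need 30 or more "participants per AD in this sample". The only prevalence given there is 3%, as an example in a statement about margin of error.

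The Discussion counts among the methodological strengths a design described as "powered to ensure we can assess the accuracy of included screening tools both for the AD as a whole, but also for each individual AD". Shortly afterwards it says that people with particular ADs are being over-sampled as required.

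The Introduction puts overall prevalence at "21% for perinatal AD". Under Research objectives in the analysis plan, accuracy for an individual AD is estimated by "comparing those who report symptoms meeting criteria for one specific AD with those whose symptoms fail to meet criteria for any AD". The Descriptive statistics section places the "receiver operating characteristic (ROC) curve analyses within the prevalence sample", a term the article does not define.

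**The concern.** The sample size section states a condition, and the Discussion reports it as a property the study already has. Nothing in between shows that the condition is met: there is no prevalence or expected count for any single AD. Accuracy for each individual AD belongs to the core objective, and the results are meant to guide practice and policy. If a less common disorder yields 15 or 20 cases, an imprecise sensitivity would be read as the result of an adequately powered analysis.

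The stated remedy is hard to place. Inclusion criteria, Recruitment, Sample representativeness and Procedures describe proportional recruitment of pregnant people across health regions, with no selection by diagnosis. Over-sampling by diagnosis must also be squared with the Discussion's description of the sample as unselected or representative, and with ROC analyses confined to a prevalence sample.

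**Working it through.** **Inputs.** From Sample size estimation: 1,000 analysed per time point, 1,200 enrolled, 15% attrition, alpha 0.05, 30 cases per AD, sensitivity 0.7, 80% power, 3% as an example prevalence. The null of 0.5 is taken from the earlier sentences of that section. Sidedness is not stated, but the comparisons are worded as greater than 0.5, which reads as one-sided. Prevalences other than 3% are assumptions.

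**Step 1: reproduce the plan's own figures.** For a single proportion tested against 0.5, score-test power is Φ[((p − 0.5)√n − 1.645 × 0.5) / √(p(1 − p))].
- Group level: about 20% of 1,000 is 200 cases. At p = 0.60: (0.1 × 14.142 − 0.822) / 0.490 = 1.21, so power is 0.886. The printed 88% is reproduced, one-sided.
- Attrition: 1,000 / 0.85 = 1,177, so 1,200 is enough. 1,200 × 0.85 = 1,020.
- Individual AD, 30 cases at p = 0.70: (0.2 × 5.477 − 0.822) / 0.458 = 0.60, so power is 0.724. Other one-sided methods give 0.729 (arcsine), 0.730 (exact) and 0.772 (Wald). Two-sided power is 0.59 to 0.67. **The printed 80% is not reproduced by any of these.**
- Cases needed for 80% at 0.70, one-sided: ((1.645 × 0.5 + 0.842 × 0.458) / 0.2)² = 36.5, so 37 by the score test. Wald gives 33, and the exact test first reaches 80% at 37. Two-sided, 42 to 49 are needed.
- At p = 0.72, 30 cases give (0.22 × 5.477 − 0.822) / 0.449 = 0.85, so power is 0.803. With 30 cases, power for AUC 0.65 (Hanley-McNeil variance, two-sided) is 0.79. The section's separate sentence on AUC 0.65 and sensitivity 0.72 therefore fits 30 cases. The 0.7 in the individual-AD sentence may be a rounding of 0.72.

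**Step 2: does the sample size deliver 30 cases?** The number of cases X is binomial(N, prevalence). The table gives P(X ≥ 30).

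| Prevalence of the AD | N = 1,000 | N = 1,020 | N = 1,200 (no losses) |
|---|---|---|---|
| 2% (assumed) | 0.02 | 0.03 | 0.13 |
| 2.5% (assumed) | 0.18 | 0.21 | 0.53 |
| 3% (article's example) | 0.53 | 0.57 | 0.87 |
| 3.5% (assumed) | 0.83 | 0.86 | 0.98 |
| 4% (assumed) | 0.96 | 0.97 | >0.99 |

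At 3% and 1,000 people the expected count is 0.03 × 1,000 = 30, so reaching it is close to a coin toss. At N = 1,000, an 80% chance of 30 cases needs a prevalence of about 3.4%, and a 95% chance about 3.9%.

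**Step 3: what a shortfall costs.** Score-test power for sensitivity 0.70, one-sided, is 0.65 with 25 cases, 0.56 with 20 and 0.46 with 15.

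**The case against.** The strongest reply is that the mitigation stands in the same paragraph as the claim. The Step 2 probabilities assume no enrichment, so they show why over-sampling would be needed, not that the study will fail. The article also fixes no prevalence for any named AD, 3% is only an example, and disorders at 4% or above reach 30 cases with probability 0.96 or more. A condensed article may also leave the over-sampling method to the full protocol. All of this stands, and it limits the point to less common disorders and to the unconditional wording.

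Three stronger readings are tempting, but the documents do not support them.
- A reader might infer that postpartum counts cannot be increased, because only pregnant people are eligible. But everyone enrolled is assessed at both time points, so people over-sampled in pregnancy add postpartum cases wherever the disorder persists.
- A reader might infer that at least one AD must fall below 30, because eight disorders at 30 each make 240 against 200 to 210 people with any AD. That holds only if one specific AD means that AD alone and there is no enrichment. The text does not say alone. If comorbid cases count, 240 / 210 = 1.14 to 240 / 200 = 1.20 diagnoses per affected person would supply the total.
- A reader might infer that over-sampled people are excluded from every individual-AD result. The prevalence-sample limit is attached to the ROC analyses and the cut-point at 0.75 sensitivity, not to the sentences on sensitivity and specificity for each AD.

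**Conclusion.** The point holds in a limited form. The Discussion presents as secured a property that Sample size estimation makes conditional, and the stated sample size does not secure it for less common ADs: the chance of 30 cases among 1,000 is 0.53 at the article's 3% example, 0.18 at an assumed 2.5% and 0.02 at an assumed 2%. These figures assume binomial sampling without enrichment. Over-sampling could improve them, but as described it is not enough to support an unconditional claim, since no recruitment section provides for it. It is not shown that any particular AD will fall short.

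The second part does not depend on prevalence. Thirty cases, sensitivity 0.70 and 80% power do not fit together: one-sided power is about 72% to 77%, and lower if two-sided. This rests on reading the null as 0.5, as in the section's earlier sentences.

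**What to change.** 1. In the Discussion, say that the study is powered for the AD as a group. Individual-AD accuracy is powered only for disorders that reach the required number of cases at the time point concerned, and is otherwise descriptive, with exact confidence intervals.
2. In Sample size estimation, correct the individual-AD sentence: either restate the sensitivity target as 0.72 with 30 cases, or keep 0.70 and raise the requirement to about 33 to 37 cases, naming the test and its sidedness.
3. Say how people with particular ADs are over-sampled and which analyses include them, define the prevalence sample, and reconcile this with the description of the sample as unselected or representative.

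A pooled prenatal and postpartum estimate with participant-clustered intervals, for ADs short of the target, is optional. It would hide differences between the two periods.

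The cost is wording and a less favourable claim; no new data are needed. Recruitment was still under way when the article was written, so case counts per AD could still be tracked.

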## Data Availability

The datasets generated and/or analysed during the study will be available from the corresponding author upon reasonable request following the completion of all primary publications derived from these datasets.

## Abbreviations

AD: Anxiety and anxiety-related disorders
AG: Agoraphobia
AUC: Area under the curve
BC: British Columbia
COPE: Australian clinical practice
DSM-5: Diagnostic and statistical manual of mental disorders
LR: Likelihood ratio
NPV: Negative predictive value
OCD: Obsessive–compulsive disorder
PPV: Positive predictive value
PTSD: Posttraumatic stress disorder
PD: Panic disorder
ROC: Receiver operating characteristic
SP: Specific phobia
SAD: Social anxiety disorder
GAD: Generalized anxiety disorder
